### Dose constraints

Structures at risk such as the brain stem, optic nerves, chiasm, and spinal cord will be contoured. Dose constraints of normal tissue will be respected according to the Quantitative Analyses of Normal Tissue Effects in the Clinic (QUANTEC) recommendation [19]. Radiotolerance of adjoining structures at risk can be limiting to dose prescription and can in certain cases require a slight reduction of the abovementioned dose regimen. For healthy tissue special consideration will be given to the healthy brain, which is being defined as structure at risk (healthy brain = whole brain – sum of all PTVs).

### Target volume definition

Treatment planning MRI is conducted within seven days prior to the start of irradiation for stereotactic mask fixation and on the day of treatment for stereotactic ring fixation. To ensure a uniform target volume definition approach and in accordance with a current consensus paper by Soliman et al. [12] the resection cavity (RC) including all contrast-enhancing lesions (T1w image after gadolinium contrast) and the surgical tract will be defined as resection cavity volume (RCV). In case of partial resection or local recurrence between resection and treatment planning MRI, all tumor remnants are included in the RCV.

For HFSRT, RCV will be expanded by up to 5 mm (depending on site, up to the treating physician’s discretion) to account for microscopic invasion to generate the CTV. For SRS, RCV will be expanded by 1 mm for CTV generation. Edema is generally not included into the CTV.

For PTV formation, a 1 mm margin will be used for HFSRT and SRS with mask positioning to account for inter-fractional cavity dynamics [20] as well as potential positioning uncertainties. In SRS with stereotactic frame positioning, PTV will equal CTV.

### Follow-up

FU visits consist of regular clinical visits and MRI scans. They will be performed at 6 weeks and three, six, nine and twelve months after the end of treatment, and additionally upon request or if new symptoms develop. Clinical follow-up includes the assessment of the following parameters/data:oncologic and non-oncologic medical history: staging examinations, chronic and acute diseases, interventions, and symptomsKarnofsky performance score, BMIdisease related physical examinationdisease related symptomsoncologic and non-oncologic medication (the parameter “corticosteroid use” is also collected for the final evaluation of the therapy response done by the radiotherapist)questionnaires: EORTC QLQ-C30, EORTC QLQ-B20 and Barthel-Indexschematic assessment of the MRI scan findings (RAF): measurements of every treated lesion, measurements of possible new lesions, final evaluation of the therapy response

### Assessment of local control

FU images are interpreted by the study neuroradiologist based on the response assessment criteria as proposed by the Response Assessment in Neuro-Oncology Brain Metastases (RANO-BM) group [21], but slightly modified to accommodate the objective of this trial. Radiographical response will be measured unidimensional and will be recorded for every resected lesion. In case of tumor recurrence, the first MRI scan suspicious of tumor progression is considered as the timepoint of recurrence. The diameter of the resection cavity and possible cystic components are not measured for response assessment.

LC will be evaluated separately for every resected lesion at each follow up MRI. For the separate assessment of LC of each specific resected lesion, use of corticosteroids and clinical condition are not considered, as this could lead to a confounding of the results.

In accordance with the proposal of the RANO-BM group, resected lesions are allocated to either measurable or non-measurable disease based on their appearance on the treatment planning MRI.

Lesions are considered measurable if they fulfil all the following criteria:nodular contrast-enhancement (as component of the RC)visible on two or more axial slicesmeasurable in at least one dimension with a minimum size of 5 mm (LD)

Any other lesions are classified as non-measurable.

For response assessment, the following criteria are applied for:Measurable lesions ≥ 5 mm and < 10 mm:◦ CR = no contrast enhancement visible◦ PR = minimum 3 mm decrease in longest diameter compared to baseline (treatment planning MRI)◦ SD =  < 3 mm increase or decrease in longest diameter◦ PD = minimum 3 mm increase in longest diameter compared to nadirMeasurable lesions ≥ 10 mm:◦ CR = no contrast enhancement visible◦ PR = minimum 30% decrease in longest diameter compared to baseline (treatment planning MRI)◦ SD =  < 30% decrease or < 20% increase in longest diameter◦ PD = minimum 20% increase in longest diameter compared to nadirNon-measurable lesions:◦ Exact measurement of non-measurable lesions is not required◦ Non-measurable lesions should be classified as absent, present or unequivocal progression

The final response assessment is done by the study radiotherapist according to the following criteria:CR can only be stated if there is no corticosteroid use related to brain metastases and if the clinical status related to brain metastases is stable or improvedPR can only be stated if the corticosteroid use related to brain metastases is stable or reduced and if the clinical status related to brain metastases is stable of improvedIf SD or PD of pre-existing lesions has been stated by the study neuroradiologist, clinical information cannot induce a change in the final response assessment done by the radiotherapist

In case of suspected radiation necrosis, diagnostic strategies include repeat MRT exam within 6 weeks as well as advanced imaging techniques (perfusion MRI, 18F-FET-PET scan, APTw imaging) and ultimately surgical pathology via biopsy or resection. When radiation necrosis is suspected in a follow up imaging, interdisciplinary case discussion at a neurooncologic tumor board is mandatory.

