### Statistical considerations and sample size calculation

The underlying null hypothesis of this study is that there is no difference in terms of LC between HFSRT and SRS. The aim of the study is to provide evidence that allows to refute the null hypothesis with a certainty of at least 95% (95% CI), so that the alternative hypothesis can be considered valid. The alternative hypothesis is that HFSRT is superior to SRS in terms of LC. The underlying data for case number calculation are the prospective trials by Mahajan et al. [5] and Brown et al. [6] for SRS (pooled mean LC rate of 66% at 12 months) and our own institutional retrospective data for HFSRT [13] (mean LC rate of 88% at 12 months). The sample size calculation was performed with a two group Chi-squared test of equal proportions (odds ratio = 1). The test significance level (α) was set to 0.05. Allocating an equal number of patients to both treatment arms, 114 patients are needed to detect a superiority of HFSRT with a power of at least 80%. We estimated a dropout rate of 10%, resulting in a total number of 126 patients, and a monthly accrual of three patients. Patients will be randomized 1:1 in the two different treatment arms. Logistic regression analysis will be used to perform predefined subgroup analyses with respect to the primary endpoint.

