Histology: Radioresistant vs. radiosensitive primary.Although a radioresistant histology such as melanoma, colorectal carcinoma or sarcoma usually does not necessarily appear to have a significant impact on LC [22], Soliman et al. [23] detected a significant association between radioresistant primary and reduced LC.Preoperative tumor volume: metastases (also) resected for size vs. metastases resected for clinical complaints only.Preoperative tumor size has also been described as a significant factor influencing local recurrence [24, 25]. A uniform cut-off value was not observed, therefore the categories "resected for size" (according to our in-house standard operating procedures approx. 3 cm in diameter) and "resected for clinical complaints" were defined for this subgroup analysis.Extent of resection (assessed on the planning MRI): residual tumor vs. complete resection.As shown by El Shafie et al. [26], incomplete resection may significantly lower LC rates.Size of RC (assessed on the planning MRI): Size > median vs. ≤ median.The size of the resection cavity or the PTV volume has been demonstrated to significantly influence LC in several data sets [7, 15, 24–28], with bigger RC yielding poorer LC rates. Although absolute cut-off values differ, they are close to the median resection cavity volume / PTV volume in the respective data sets. In the SATURNUS trial, the size of the PTV is also dependent on the allocation to the treatment arm and positioning method. Therefore, the extent of the RC is the more appropriate stratification factor for this subgroup analysis.Number of brain metastases: > 1 vs. 1As shown by Eitz et al. [15] > 1 metastasis present can have a significantly negative impact on LC.Extracranial disease status: uncontrolled primary tumor vs. controlled primary tumor at time of Screening Visit.In the multi-institutional analysis by Eitz et al. [15], an uncontrolled primary tumor yielded poorer LC rates.Dose: Margin dose < 48 Gy BED10 vs. >48 Gy BED10.

There are a couple of analyses [24, 28, 29] showing a significant impact of delivered dose on LC. As 48 Gy BED10 has been demonstrated as cut-off value in two independent data sets [28, 29], this threshold is also used in the subgroup analysis.

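### Local control is worded and scored per resected lesion but sized and populated per patient; no rule links the two units, and the lesion-level analyses make no allowance for within-patient correlation.

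*Protocol article*

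**What the plan says.** Places that point to lesions, all in the protocol article:

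- Primary endpoint and Secondary endpoints: both LC rates at 12 months are worded over sites, first the resected ones, then all treated ones.
- Inclusion criteria: one to three resected metastases per patient. Trial population allows further, unresected metastases, and no upper limit on their number is stated.
- Assessment of local control: "LC will be evaluated separately for every resected lesion at each follow up MRI".
- Subgroup analyses: the factors include reason for resection ("metastases (also) resected for size vs. metastases resected for clinical complaints only"), extent of resection, cavity size and margin dose. The closing paragraph equates the primary endpoint with LC of the resected metastases and adds exploratory associations with isodose line and PTV dose metrics.

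Places that point to patients:

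- Statistical considerations and sample size calculation: a two-group chi-squared test comparing "pooled mean LC rate of 66% at 12 months" (SRS) with "mean LC rate of 88% at 12 months" (HFSRT). "The test significance level (α) was set to 0.05". The count is obtained by "Allocating an equal number of patients to both treatment arms" and comes to 114, or 126 with dropout.
- Analysis plan: the intention-to-treat population consists of all randomized patients.

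On the model: "Logistic regression analysis will be used to perform predefined subgroup analyses with respect to the primary endpoint". No within-patient term is mentioned there or under Subgroup analyses.

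**The concern.** A rate needs a denominator, and the article supports two. Someone following the endpoint wording and the per-lesion scoring would count lesions. Someone following the sample size and the analysis population would count patients. The two give different estimates for anyone with more than one resected lesion, and only the patient count satisfies the independence that the chi-squared calculation assumes.

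Two things are at stake. First, the unit of the primary endpoint could be settled after outcomes are known, in a trial where only the study neuroradiologist is blinded. Second, where lesions are the natural unit (lesion-level subgroups, all treated sites, dose associations), a logistic model without allowance for correlation gives wrong standard errors.

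**Working it through.** **1. Reproduce the plan's figure.** Inputs from the sample size section: 66% vs 88%, alpha 0.05, power at least 80%, 1:1. Sidedness is not stated. Two-sided without continuity correction gives 57 per arm, 114 in total, with power 80.5%. The stated 114 is reproduced exactly and corresponds to one independent outcome per patient.

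**2. Arm comparison if resected lesions were pooled as independent.** With m lesions per patient and intraclass correlation ICC:

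- design effect DE = 1 + (E[m²]/E[m] − 1) × ICC
- naive interval width relative to correct = 1/√DE
- actual two-sided type I error = 2 × (1 − Φ(1.96/√DE))

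The documents give neither the lesion mix nor the ICC, so both are assumptions.

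Example: 75/20/5% of patients with 1/2/3 lesions. E[m] = 0.75 + 0.40 + 0.15 = 1.30. E[m²] = 0.75 + 0.80 + 0.45 = 2.00. The ratio is 1.538.

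| Mix (1/2/3 lesions) | ICC | DE | Naive width | Type I error |
|---|---|---|---|---|
| 90/9/1% | 0.2 | 1.043 | 0.98 | 5.5% |
| 90/9/1% | 0.4 | 1.086 | 0.96 | 6.0% |
| 75/20/5% | 0.2 | 1.108 | 0.95 | 6.3% |
| 75/20/5% | 0.4 | 1.215 | 0.91 | 7.5% |

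Beta-binomial simulation (63 per arm, 77% LC in both arms) agrees, at about 5.4 to 7.7%. A heavier assumed mix of 70/20/10% with ICC 0.5 gives DE 1.357 and 9.3%. A lighter one, 90/9/1% with ICC 0.1, gives 5.3%.

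**3. All treated sites.** With exactly 3 sites per patient (assumed), DE = 1 + 2 × ICC. ICC 0.2 gives 1.4 and a type I error of 9.8%; ICC 0.4 gives 1.8 and 14.4%. Uneven counts raise this. Simulation with a mean near 2.7 and a range of 1 to 10 sites gives about 13 to 20%. The formula agrees if E[m²]/E[m] is about 4.35: DE is 1 + 3.35 × 0.2 = 1.67 (12.9%) and 1 + 3.35 × 0.4 = 2.34 (20.0%).

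**4. Factors that vary within a patient.** Take the limiting case of two lesions in each patient, one with residual tumor and one without. The variance of the within-pair difference is 2p(1−p)(1−ICC), while the naive variance is 2p(1−p). The naive interval is then 1/√(1−ICC) times the correct one: 1/√0.8 = 1.12 at ICC 0.2 and 1/√0.6 = 1.29 at ICC 0.4. Here it is too wide, not too narrow.

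**5. The unit changes the quantity estimated.** With the 75/20/5% mix, lesion rates of 66% and 88%, and a beta-binomial model, the share of patients controlled at all resected sites is:

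- ICC 0.2, SRS: 0.75 × 0.66 + 0.20 × 0.480 + 0.05 × 0.372 = 61%
- ICC 0.2, HFSRT: 0.75 × 0.88 + 0.20 × 0.796 + 0.05 × 0.732 = 86%
- ICC 0.4: 62% and 86%

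The absolute difference is 24 to 25 points, against 22 per lesion.

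**The case against.** The strongest reply is that the analysis passages already point to patients. The sample size and the intention-to-treat set are in patients, and 57 per arm is exactly what one outcome per patient requires. Reading each lesion separately on MRI is needed for a patient-level outcome too, so it does not by itself fix the denominator. The article condenses a full protocol, and the choice of GEE or robust variance is commonly left to a SAP, which is not shown.

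Much of this stands, and it rules out several stronger readings that a reader might infer:

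- *That the primary comparison is a naive lesion-level logistic regression with inflated type I error.* Logistic regression is named only for subgroup analyses, nothing calls it ordinary, and nothing says lesions are treated as independent. The inflation is conditional on pooling.
- *That the subgroup regressions have to run on lesions.* A patient-level covariate could be defined, such as any residual tumor or the largest cavity. Histology, number of metastases and extracranial status are patient-level already.
- *That ignoring clustering always makes intervals too narrow.* Step 4 of the working shows the reverse for factors varying within a patient.
- *That including unresected lesions in the all-sites endpoint is an error because it dilutes the arm contrast.* That is a preference about a secondary endpoint. The resected-only rate is already primary, and LC of non-resected metastases is named separately.

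What the reply does not remove is the gap in the endpoint definition. The article does define its primary endpoint, and it does so over sites. It nowhere says how two or three lesion results combine. That is more than a modelling detail left for later.

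**Conclusion.** The point holds in limited form. The unit of the LC endpoints is not fixed: wording and scoring are per lesion, sizing and analysis population are per patient, and no rule connects them. The lesion-level analyses name a model with no allowance for within-patient correlation.

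The consequence depends on the reading. With a patient-level primary test there is no inflation and the 114 is unaffected. If lesions are pooled as independent, the type I error of the arm comparison is about 5.4 to 7.7% for resected sites, a modest excess, and about 13 to 20% for all treated sites, which is a secondary endpoint. These figures rest on assumed lesion mixes, an assumed mean near 2.7 treated sites with uneven counts, and ICC 0.2 to 0.4. For lesion-varying factors the error can run the other way. The plan should be changed, but the finding does not show that the sample size is wrong.

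**What to change.** State the primary endpoint per patient: LC at 12 months means control at all resected sites, and it is lost at the first failure of any of them. This matches the patient-based sample size and analysis set.

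Run every lesion-level analysis (subgroups by lesion-level factors, LC at all treated sites, dose associations) with GEE or patient-clustered robust variance.

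The cost is wording in the protocol or SAP, with no extra patients or scans. Patient-level LC will be slightly lower than lesion-level LC (step 5 of the working: about 61 to 62% against 66%, and 86% against 88%, under the assumed mix), and some lesion-level intervals will be a little wider.

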### Statistical considerations and sample size calculation

The underlying null hypothesis of this study is that there is no difference in terms of LC between HFSRT and SRS. The aim of the study is to provide evidence that allows to refute the null hypothesis with a certainty of at least 95% (95% CI), so that the alternative hypothesis can be considered valid. The alternative hypothesis is that HFSRT is superior to SRS in terms of LC. The underlying data for case number calculation are the prospective trials by Mahajan et al. [5] and Brown et al. [6] for SRS (pooled mean LC rate of 66% at 12 months) and our own institutional retrospective data for HFSRT [13] (mean LC rate of 88% at 12 months). The sample size calculation was performed with a two group Chi-squared test of equal proportions (odds ratio = 1). The test significance level (α) was set to 0.05. Allocating an equal number of patients to both treatment arms, 114 patients are needed to detect a superiority of HFSRT with a power of at least 80%. We estimated a dropout rate of 10%, resulting in a total number of 126 patients, and a monthly accrual of three patients. Patients will be randomized 1:1 in the two different treatment arms. Logistic regression analysis will be used to perform predefined subgroup analyses with respect to the primary endpoint.

### Analysis plan

The primary analysis will be based on the full analysis set which is according to the intention-to-treat principle. The Intention to treat Population includes all patients that were randomized into one of the treatment arms, disregarding the actual treatment, possible non-compliance or withdrawal that may happen after randomization. We have chosen this approach as the method of primary analysis because it better reflects actual clinical processes, knowing that the analysis results concerning the treatment effect are more likely to be conservative.

Interim Analysis: An interim analysis is planned after the first 40 patients have been treated and followed up for 12 months. It mainly serves as a safety analysis. SAEs and AEs in both treatment arms will be compared. A statistically significant difference in SAEs related and probably related to the study therapy between the treatment arms will lead to a premature closure of the study.

### Subgroup analyses

Apart from fractionation schemes, there exist other parameters that might influence LC after RC irradiation. To evaluate possible further influencing factors, the PubMed database (https://pubmed.ncbi.nlm.nih.gov) was searched for the combined criteria "brain metastases", "resection cavity irradiation" and "local control". The literature search yielded 137 articles. After abstract review, 13 articles remained that appeared suitable to deliver relevant information, all retrospective in nature. There is no parameter that has consistently been demonstrated as a significant influencing factor on LC. However, those factors that showed a significant influence of LC in at least one dataset have been included as stratification factors for subgroup analyses. Subgroup analyses will be carried out using logistic regression analysis. The influencing factors identified are listed below, together with the supporting literature:

Histology: Radioresistant vs. radiosensitive primary.Although a radioresistant histology such as melanoma, colorectal carcinoma or sarcoma usually does not necessarily appear to have a significant impact on LC [22], Soliman et al. [23] detected a significant association between radioresistant primary and reduced LC.Preoperative tumor volume: metastases (also) resected for size vs. metastases resected for clinical complaints only.Preoperative tumor size has also been described as a significant factor influencing local recurrence [24, 25]. A uniform cut-off value was not observed, therefore the categories "resected for size" (according to our in-house standard operating procedures approx. 3 cm in diameter) and "resected for clinical complaints" were defined for this subgroup analysis.Extent of resection (assessed on the planning MRI): residual tumor vs. complete resection.As shown by El Shafie et al. [26], incomplete resection may significantly lower LC rates.Size of RC (assessed on the planning MRI): Size > median vs. ≤ median.The size of the resection cavity or the PTV volume has been demonstrated to significantly influence LC in several data sets [7, 15, 24–28], with bigger RC yielding poorer LC rates. Although absolute cut-off values differ, they are close to the median resection cavity volume / PTV volume in the respective data sets. In the SATURNUS trial, the size of the PTV is also dependent on the allocation to the treatment arm and positioning method. Therefore, the extent of the RC is the more appropriate stratification factor for this subgroup analysis.Number of brain metastases: > 1 vs. 1As shown by Eitz et al. [15] > 1 metastasis present can have a significantly negative impact on LC.Extracranial disease status: uncontrolled primary tumor vs. controlled primary tumor at time of Screening Visit.In the multi-institutional analysis by Eitz et al. [15], an uncontrolled primary tumor yielded poorer LC rates.Dose: Margin dose < 48 Gy BED10 vs. >48 Gy BED10.

There are a couple of analyses [24, 28, 29] showing a significant impact of delivered dose on LC. As 48 Gy BED10 has been demonstrated as cut-off value in two independent data sets [28, 29], this threshold is also used in the subgroup analysis.

Regarding the primary endpoint (LC of resected metastases) as well as LC of non-resected metastases, it will be analyzed exploratory whether an association between LC rate and prescription IDL as well as Dmax, Dmean and Dmin of the PTV can be observed. For the secondary endpoints LRC, OS and development of radionecrosis and pseudoprogression, possible influencing factors will be analyzed exploratively.

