### Trial design

The trial is designed as a prospective, randomized, controlled, monocentric phase III trial. It is conducted at the academic hospital Klinikum rechts der Isar of the Technical University of Munich, Germany. A flow chart of the study is provided in Fig. 1. Patients fulfilling the above criteria are considered for study participation and participants are randomly 1:1 allocated to either adjuvant HFSRT (6 – 7 × 5 Gy i.e., 30 Gy/6 fractions or 35 Gy/7fractions; Arm A) or SRS (1 × 12–20 Gy; Arm B). In case a higher dose is needed for adequate tumor control (at the discretion of the treating physician), the maximum allowed dose depends on the cavity diameter and does equivalate the findings of the RTOG 90–05 trial (24 Gy, 18 Gy, and 15 Gy for tumors ≤ 20 mm, 21–30 mm, and 31–40 mm in maximum diameter) [17]. Unresected brain metastases, if present, are treated with SRS (1 × 14 – 22 Gy, prescribed to the surrounding isodose). The affiliation to the treatment arm will not be blinded to anyone except the study neuroradiologist.

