### Dose prescription

Arm A HFSRT: 6 – 7 × 5 Gy prescribed to the surrounding isodoseRationale: Dose regimen is analogous to the own institutional data by Specht et al. [13] yielding excellent local control rates after adjuvant stereotactic irradiation with 7 x 5 Gy on which the sample size calculation is based (see below). It has been shown that 6 x 5 Gy and 7 x 5 Gy lead to comparable tumor control rates in adjuvant stereotactic irradiation of the resection cavity [14], and therefore dose de-escalation to 6 x 5 Gy may be allowed, if desired/needed for protection of structures at riskArm B SRS: 1 × 12-20 Gy prescribed to the surrounding isodose, depending on cavity size and proximity to structures at risk.Rationale: Dose regimen for SRS are analogous to the dose regimen applied in the phase III trials by Mahajan et al. [5] and Brown et al. [6], on which the sample size calculation is based (see below). Mahajan et al. applied SRS with 1 x 12-16 Gy, whereas Brown et al. delivered postoperative SRS with 1 x 15-20 Gy.In case a higher dose is needed for adequate tumor control (at the discretion of the treating physician), the maximum allowed dose depends on the cavity diameter and does equivalate the findings of the RTOG 90-05 trial (24 Gy, 18 Gy, and 15 Gy for tumors ≤ 20 mm, 21-30 mm, and 31-40 mm in maximum diameter, respectively) [18]Unresected brain metastases, if present, are treated with SRS: 1 × 14 – 22 Gy prescribed to the surrounding isodose. In individual cases (e.g., metastasis near the brain stem), a fractionated approach with, for example, 6 × 5 Gy may be necessary.

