The SATURNUS study is a prospective, randomized, controlled phase III trial at this point of time planned as a monocentric study that seeks to accrue 126 patients with up to three resected brain metastases to receive adjuvant stereotactic irradiation. It aims to determine the optimal fractionation scheme (HSFRT vs. SFRT) regarding local tumor control. Side effects, among others, are evaluated as secondary endpoints. The SATURNUS study is based on the hypothesis of the superiority of HFSRT to SRS regarding LC, based on our own institutional data [13] on HFSRT in comparison with the available prospective phase III data on SRS [5, 6]. To also consider other possible influencing factors on LC, the SATURNUS study included a broad subgroup analysis of factors identified in a literature search. One of these factors, among many others, is radiation dose. We provided the rationale for the dose schemes allowed within the study yet acknowledge that the dose prescriptions allowed within the study are broad, especially for SRS. Some retrospective analyses, for both SRS and HFSRT, observe no significant effect of dose on local control [14, 15, 23, 26, 32–34]. On the other hand, in the prospective phase III trail by Mahajan et al. [5], LC was observed to be significantly lower with larger cavities. As per protocol, larger cavities receive less dose. However, it can only be postulated that the lower doses delivered are actually the reason for this. Larger cavity size has been found to be associated with higher local failure rates in some retrospective analyses [29, 32, 34]. The rather broad dose corridors allowed within the study represent a potential limitation of the study, yet this issue will be addressed in a predefined subgroup analysis, as well as the cavity size. Addressing further limitations of the study, a possible confounding variable might also be the variation in margins. A resection cavity to CTV margin is constantly applied, yet for HFSRT the expansion might not necessarily be uniform for every patient, depending on the site of the resection cavity. In accordance with clinical practice, smaller safety margins are applied for SRS than for HFSRT. This factor might also be responsible for the relatively higher local failure rate in the single-dose trials [5, 6].

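### The predefined 48 Gy BED10 dose subgroup is set after randomisation, so its strata do not hold comparable patients in the two arms

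*Protocol article*

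**What the plan says.** The sample size section states: "Logistic regression analysis will be used to perform predefined subgroup analyses with respect to the primary endpoint". Under Subgroup analyses, factors that were significant in at least one dataset "have been included as stratification factors for subgroup analyses". Seven are listed. Six describe the patient, the tumour or the cavity before irradiation. The seventh is "Margin dose < 48 Gy BED10 vs. >48 Gy BED10".

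The dose menus differ by arm. Trial design gives HFSRT as "6 – 7 × 5 Gy i.e., 30 Gy/6 fractions or 35 Gy/7fractions; Arm A". Dose prescription allows the lower HFSRT schedule in order to protect structures at risk. It gives SRS as 1 × 12–20 Gy, "prescribed to the surrounding isodose, depending on cavity size and proximity to structures at risk".

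On cavity size, Subgroup analyses reports poorer local control with larger cavities. It prefers resection cavity size to PTV size because "the size of the PTV is also dependent on the allocation to the treatment arm and positioning method".

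The Discussion calls the broad dose corridors a potential limitation and continues: "yet this issue will be addressed in a predefined subgroup analysis, as well as the cavity size".

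**The concern.** A subgroup comparison of randomised arms keeps the protection of randomisation only if the subgroup is defined by something that allocation cannot influence. Margin dose fails that test. The same patient, with the same cavity, could fall above the cut in one arm and below it in the other, purely because the arms use different schedules and different reasons for choosing among them. Cavity size is one of those reasons in the SRS arm, and the protocol itself treats it as prognostic.

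The protocol applies this reasoning to PTV size but not to dose. It then relies on the dose subgroup to deal with a limitation it acknowledges. A reader of the results could take a difference between dose strata as evidence that the benefit of HFSRT depends on dose, when it reflects which patients were placed in each stratum.

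**Working it through.** **1. The sample size is not in dispute.** For 88% vs 66%, two-sided α 0.05, 80% power and no continuity correction:

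n per arm = [1.96·√(2·0.77·0.23) + 0.842·√(0.88·0.12 + 0.66·0.34)]² / 0.22² ≈ 56.3, rounded up to 57, so 114 in total as stated.

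**2. Where the cut falls.** BED10 = nd(1 + d/10), with schedules from Trial design and Dose prescription.

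| Schedule | BED10 (Gy) | Side of 48 |
|---|---|---|
| HFSRT 6 × 5 Gy | 30 × 1.5 = 45.0 | below |
| HFSRT 7 × 5 Gy | 35 × 1.5 = 52.5 | above |
| SRS 12 Gy | 12 × 2.2 = 26.4 | below |
| SRS 15 Gy | 15 × 2.5 = 37.5 | below |
| SRS 17 Gy | 17 × 2.7 = 45.9 | below |
| SRS 18 Gy | 18 × 2.8 = 50.4 | above |
| SRS 20 Gy | 20 × 3.0 = 60.0 | above |

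The single dose with BED10 = 48 solves d² + 10d − 480 = 0, so d = (−10 + √2020)/2 = 17.47 Gy.

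In the HFSRT arm the cut is thus the choice between the two listed schedules, driven by structures at risk. In the SRS arm it is below or above about 17.5 Gy, driven by cavity size and structures at risk.

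**3. A hand illustration with no arm or dose effect.** Assumptions, none from the protocol: local control 90% for cavities up to 30 mm and 70% for larger ones; half of cavities larger; half of the small SRS cavities given 18 Gy or more and no large ones; 6 × 5 Gy chosen independently of size.

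- Above 48: SRS 90%; HFSRT 0.5·90 + 0.5·70 = 80%. Difference −10 points for HFSRT.
- Below 48: SRS (0.50·70 + 0.25·90)/0.75 = 76.7%; HFSRT 80%. Difference +3.3 points.

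The strata differ by about 13 points and change sign although neither arm nor dose has any effect.

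**4. A range under other assumptions.** Large simulation (2 million patients per scenario): 20/40/40% of cavities at ≤20, 21–30 and 31–40 mm; 30% near structures at risk, independent of size; HFSRT above the cut unless near such structures; SRS above the cut if ≤30 mm and not near them; local control 66% without an arm effect; no dose effect. This puts 70% of the HFSRT arm and 0.6 × 0.7 = 42% of the SRS arm above the cut. The log-odds of control fall by 0.7 or 1.0 per size class and by 0 to 0.7 near structures at risk.

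| True arm OR | OR above 48 | OR below 48 | Ratio of ORs |
|---|---|---|---|
| 1.0 | 0.56–0.68 | 1.02–1.41 | 0.40–0.66 |
| 3.78 (88% vs 66%) | 1.93–2.42 | 3.46–4.88 | 0.40–0.67 |
| Either, size and location not prognostic | equals true OR | equals true OR | 0.99–1.01 |

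The last row shows that selection alone produces the apparent interaction.

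**5. What adjustment can do.** In step 3, local control within a size class is the same in every arm and dose cell, so adding that size class to the model removes the whole 13 points. In step 4, size alone is not enough when location is prognostic: among 31–40 mm cavities, the stratum below 48 holds every SRS patient but only those HFSRT patients near structures at risk. Proximity to such structures is not among the seven listed factors.

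**The case against.** The strongest reply is that the protocol never specifies the analysis being criticised. The section introduces the list as parameters, other than fractionation, that may influence local control. That can be read as a search for prognostic factors, and no interaction term or within-stratum arm contrast is stated. A reader might infer that an unadjusted HFSRT-versus-SRS comparison by dose is prescribed; the text does not go that far. Nor can one say that the analysis is unable to separate dose from cavity size. Logistic regression can carry arm and cavity size as covariates, cavity size is already a listed factor, and the model's terms may be set in an analysis plan that is not shown.

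Three further inferences should be resisted:

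- **SRS cavities of 31–40 mm can never exceed the cut.** The 15 Gy limit for that size would imply this, but it is introduced only for cases needing a higher dose. Whether the diameter limits bind within the ordinary 12–20 Gy range is unclear.
- **The cut contradicts the statement that "6 x 5 Gy and 7 x 5 Gy lead to comparable tumor control rates in adjuvant stereotactic irradiation of the resection cavity".** It does not. The protocol admits any factor significant in at least one dataset while saying that none is consistent.
- **The protocol overlooks the issue.** The Discussion concedes, for an earlier phase III trial, that lower dose in larger cavities could only be postulated as the cause of poorer control.

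What remains is that either reading has the problem. As an effect modifier, dose is a post-randomisation variable. As a prognostic factor, it is entangled with arm, cavity size and location, and the one-factor dose split as listed does nothing about that.

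**Conclusion.** The point holds in limited form. Margin dose at 48 Gy BED10 is set after randomisation, by arm-specific menus and for reasons that differ by arm, so it does not belong with baseline factors as a treatment-effect subgroup. Within-stratum arm contrasts would not be randomised comparisons and can show a spurious interaction. A prognostic reading needs adjustment for arm, cavity size and location.

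The mechanism follows from the protocol's own dose rules and its statement on cavity size. The size of the bias does not: the 13-point example and the odds-ratio ratios of 0.40 to 0.67 rest on cavity, location and outcome distributions that the protocol does not give. They are illustrations, not estimates for this trial. A reader might also infer that the main result is at risk. It is not: the intention-to-treat primary comparison and the 114/126 sample size are unaffected.

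**What to change.** - Remove BED10 from the predefined treatment-effect subgroups. Keep resection cavity size on the planning MRI, already listed, for that purpose.
- Report dose as a non-randomised exploratory analysis beside the prescription-isodose and Dmax/Dmean/Dmin analyses at the end of Subgroup analyses. Do it within each arm: 6 × 5 vs 7 × 5 Gy in the HFSRT arm, which has only two standard values, and dose as a continuous variable in the SRS arm. Adjust for cavity size and proximity to structures at risk, and record that proximity for each patient if it is not already captured.
- Amend the Discussion so that it no longer says this subgroup analysis deals with the dose-corridor limitation.

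The cost is essentially wording. With about 63 patients per arm (126/2), the within-arm dose analyses will be imprecise and should be labelled so. No dose, clinical rule, sample size or primary analysis changes.
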